	• To identify the perceived benefit and value of KT tools for this population, including important components that enhance knowledge about childhood AGE and decision-making regarding choice to take child with AGE to the ED.
Process domain	• To identify whether using an electronic, web-based platform for intervention delivery and data collection is feasible with this population.
Management domain	• To describe this population’s willingness to participate in future, similar research (i.e., full-scale trial).
Resource domain	• To estimate time required for participants to complete data collection forms.
	• To identify whether using iPads to collect data is feasible with this population.

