### Study location and population

The study will be conducted at one Canadian, tertiary care, pediatric hospital. Parents meeting the eligibility criteria in Table 2 will be invited to participate.

**Table 2 Tab2:** Study eligibility criteria

Study eligibility criteria	
Inclusion criteria	1. Parent or caregiver of a child 16 years old or younger.
	2. Child is presenting to the ED with vomiting and diarrhea.
	3. Parent is fluent in English.
	4. Parent is willing to be contacted for follow-up data collection.
Exclusion criteria	1. Child has significant chronic gastrointestinal problem or inflammatory bowel disease (i.e., Crohn’s disease, inflammatory bowel disease, ulcerative colitis, chronic constipation).
	2. Child is taking immunosuppressive therapy or known history of immunodeficiency.
	3. Child has undergone oral or gastrointestinal surgery within the preceding 7 days.
	4. Child has had a prior visit to the ED for vomiting and diarrhea within the preceding 14 days.

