	*Quantitative*: MCIDs will be calculated for the parental knowledge questionnaire and the decision regret scale using two methods: (1) data-driven approach and (2) patient-perspective [58].	Using a data driven approach, the standard error of measurement will be used as a proxy for the MCID. Using a patient perspective, patients will make global ratings on their own change via Likert items in post-intervention questionnaires 1 and 2. Both approaches will be compared to quantified changes in outcome measures and absolute change for both will be calculated [58].
	*Quantitative*: Post-ED healthcare utilization will be assessed by three items developed by the research team.	Descriptive statistics will be calculated.
	*Quantitative*: The perceived benefit and value of the KT intervention for pediatric AGE will be evaluated using four items developed by the research team and by examining the number of participants that request a video link after questionnaire 1.	Descriptive statistics will be calculated.
	*Qualitative*: The perceived benefit and value of the KT intervention for pediatric AGE will be also evaluated via a qualitative interview with a convenience sample of volunteer parents from the experimental intervention group.	Thematic analysis of interview data will be conducted.
Process domain	*Quantitative*: Consent rate will be measured by (1) percentage of people approached who consent to participate and (2) timing (date, time of day) of refusals.	Descriptive statistics will be calculated.
	*Quantitative*: Recruitment rate will be measured by (1) percentage of people who consented to participate and complete pre-intervention questionnaire, post-intervention questionnaire 1, post intervention questionnaire 2, and qualitative interview; and (2) timing (date, time of day) of recruitment.	Descriptive statistics will be calculated.
	*Quantitative*: Data completion will be measured by (1) percentage of missing/blank survey items and (2) percentage of drop-outs at post-intervention questionnaire 2.	Descriptive statistics will be calculated.
	*Qualitative*: Satisfaction with electronic platform will be evaluated in the qualitative semi-structured interview with a convenience sample of volunteer parents from the experimental intervention group.	Thematic analysis of interview data will be conducted.

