Management domain	*Quantitative*: Data quality will be measured by number, type, and duration of technical problems (i.e., error messages, problems with internet connectivity, and lost data) with an online platform throughout the study period.	Descriptive statistics will be calculated.
	*Qualitative*: Parents’ willingness to participate in future, similar research will be evaluated by a qualitative interview with a convenience sample of volunteer parents from the experimental intervention group.	Thematic analysis of interview data will be conducted.
Resource domain	*Quantitative*: Time to collect data will be measured by (1) average length of time to complete study questionnaires and (2) average length of time (days) to complete post-intervention questionnaire 2 post-discharge.	Descriptive statistics will be calculated.
	*Quantitative*: The feasibility of using iPads to collect data in the ED with parents/caregivers will be measured by tracking the number of broken, lost, or stolen iPads, iPad chargers (including cord and plug), iPad cases, and WiFi hubs.	Descriptive statistics will be calculated.

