### Data collection

Participants will be provided with disposable headphones and an iPad containing the iCare Adventure electronic platform. iCare Adventure is a client-server based e-therapeutics platform designed to expedite and improve the management of patients’ care within pediatric ED facilities. iPads, which are locked to the iCare Adventure app, are given to parents participating in research in the ED. All content within the app, including screen flow, textual content, images, videos, protocols, and questionnaires, is controlled on a centralized server. When the application restarts, it calls to the server, the iPads report all user interactions back to the server in real time, and the server can dynamically create real-time reports of the aggregated data. Data collection processes and forms will be piloted with the research team prior to the start of data collection.

The informed consent process and quantitative data collection will be completed on iCare Adventure, and participants will be automatically given the questionnaires and appropriate intervention (i.e., whiteboard video or sham video) based on the randomization sequence. A unique study identifier will be generated for each participant within the iCare Adventure platform. All data collection points will be electronically time-stamped.

As part of the post-intervention questionnaire 1, participants receiving the experimental intervention will be asked about their willingness to be contacted later for an individual, in-depth, semi-structured, qualitative interview. If interested, they will provide contact information (i.e., name, phone number, and best time to contact) and a member of the research team will follow up via telephone.

Using a qualitative descriptive approach [37, 38], a semi-structured interview guide will be used. This data collection strategy will be used to obtain all information required, probe participants’ responses, and give participants freedom to respond and illustrate concepts in an open-ended fashion [36]. Interview questions will move from the general to the specific, with interviews later in the data collection period becoming increasingly more focused [39]. Interviews will be conducted in-person or over the telephone and will be audio recorded. Audio recordings will be anonymized, de-identified, and transcribed verbatim by a third party contractor. Transcriptionists will sign a confidentiality agreement.

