The following data will be collected over the course of this study:Pre-intervention questionnaire (baseline, see Additional file 1): Participants will complete a pre-intervention questionnaire that includes demographics, knowledge questionnaire, and Decision Regret Scale within the iCare Adventure platform on the iPad.**Participants will then be randomized to view the study intervention or the standard care intervention within the iCare Adventure platform on the iPad. This process will be seamless for the participants.Post-intervention questionnaire 1 (immediate, see Additional file 2): After viewing the intervention, participants will complete the knowledge questionnaire and Decision Regret Scale a second time. In addition, participants will complete two items assessing their own performance on the knowledge questionnaire and Decision Regret Scale and one item regarding the perceived value and benefit of the KT tool. They will also be asked if they would like a video link emailed to them. At the end of this questionnaire, parents will be informed that the post-intervention questionnaire 2 will be emailed to them 4 days after this ED visit for completion at their earliest convenience. Experimental intervention group parents will be asked about participation in a qualitative focus group at this time.Post-intervention questionnaire 2 (4–14 days post-ED, see Additional file 3): Participants will be emailed a secure link on day 4 post-ED discharge to complete the knowledge questionnaire and Decision Regret Scale a third time, two items assessing their own performance on the knowledge questionnaire and Decision Regret Scale, three items related to healthcare utilization, and three items related to the perceived value and benefit of the KT tool (if applicable). Reminders to complete post-intervention questionnaire 2 will be sent to those who have not completed the survey every third day (day 7, 10, 13) to complete the survey by day 14 post ED-discharge. Previous research has demonstrated that 82% of AGE cases are resolved in 3 days or less and 14 days [40] represents the outer limit for pediatric AGE resolution [41].Post-intervention semi-structured interview (sub-sample of experimental group, see Additional file 4): Participants in the experimental group indicating willingness to participate in an in-depth, semi-structured, qualitative interview will be contacted via telephone after completion of post-intervention questionnaire 2. Up to three phone calls will be made to establish interview date/time. Qualitative interviews will focus on satisfaction with iCare Adventure platform, perceived benefit and value of the KT intervention, and willingness to participate in future, similar research.

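### Willingness to join a full-scale trial is an aim for the whole population, but it is asked directly only of interview volunteers in the experimental arm

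*Protocol article*

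**What the plan says.** The management objective in Table 1 (Background) concerns the population's "willingness to participate in future, similar research (i.e., full-scale trial"). In Table 3 (Outcomes) the only entry for this objective states that "willingness to participate in future, similar research will be evaluated by a qualitative interview with a convenience sample of volunteer parents"; these volunteers are drawn only from the arm shown the whiteboard video, and the analysis is thematic.

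Table 3 handles one process-domain measure in the same way: "Satisfaction with electronic platform will be evaluated in the qualitative semi-structured interview with a convenience sample of volunteer parents from the experimental intervention group". The Table 1 objective above that measure is broader: "To identify whether using an electronic, web-based platform for intervention delivery and data collection is feasible with this population".

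The route to an interview is set out in three places:
- Eligibility (Table 2): "Parent is willing to be contacted for follow-up data collection".
- Questionnaire 1 (Data collection): "participants receiving the experimental intervention will be asked about their willingness to be contacted later for an individual, in-depth, semi-structured, qualitative interview".
- After follow-up (Data collection): willing parents "will be contacted via telephone after completion of post-intervention questionnaire 2", with at most three calls.

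The section on sample size expects 12–20 interviews, and about 500 AGE presentations at the site in six months.

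**The concern.** The aim is a description of a population, while the direct evidence comes from a small group chosen by steps that resemble the outcome. A parent who has agreed to an additional research interview has already shown a readiness to take part in research. Parents in the sham arm use the same iPad platform, and their readiness to accept randomisation to a hand-washing video matters as much to a future two-arm trial, yet they are never asked.

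The pilot exists to inform the design of the full-scale trial. If the interview findings were read as the population's view, the planners could be too optimistic about recruitment, and would have no stated opinion from the control condition to check against.

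**Working it through.** The plan states no figure for this aim, so there is none to reproduce. The check follows who can contribute a direct answer, and then illustrates the direction of the selection.

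**Who is asked.** To be interviewed, a parent must:
1. accept follow-up contact (Table 2) and consent;
2. be randomised to the experimental arm;
3. opt in to interview contact during questionnaire 1;
4. complete questionnaire 2;
5. be reached within three calls.

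Step 2 removes the whole sham arm, step 3 the interview decliners and step 4 the drop-outs.

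**Whether another item offsets this.** As listed under Data collection, questionnaire 1 holds the knowledge questionnaire, the Decision Regret Scale, two self-rating items, one item on the value of the tool and the video-link request. Questionnaire 2 repeats the two scales and the self-ratings, and adds three utilisation items and three value items. The pre-intervention questionnaire holds demographics and the two scales. None of these lists includes willingness for future research or satisfaction with the platform.

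**Coverage.** The inputs are 12–20 interviews and about 500 presentations.
- Share of presenting families: 12/500 = 2.4% to 20/500 = 4.0%.
- Share of the experimental arm if all 500 enrolled 1:1 (an upper bound on enrolment): 12/250 = 4.8% to 20/250 = 8.0%.
- Share of the experimental arm if 100 were randomised (assumption): 12/50 = 24% to 20/50 = 40%.
- Share of the sham arm: none, whatever the enrolment.

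**Direction of the bias.** Let p be true willingness among enrolled parents, and r the chance that a willing parent reaches interview divided by the chance that an unwilling one does. Apparent willingness among interviewees is then

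pr / (pr + 1 − p).

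Both p and r are assumptions, because the protocol gives neither.

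| p | r = 1 | r = 2 | r = 5 | r = 10 |
|---|---|---|---|---|
| 40% | 40% | 57% | 77% | 87% |
| 50% | 50% | 67% | 83% | 91% |
| 70% | 70% | 82% | 92% | 96% |

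For example, with p = 0.5 and r = 2: 1.0/(1.0 + 0.5) = 67%. The shift is upward whenever r exceeds 1, which is plausible because step 3 is itself consent to more research. Its size depends entirely on r.

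**The case against.** The strongest defence is that willingness and platform feasibility are also observed in other ways. Table 3 records the percentage of those approached who consent, and when refusals occur. That is actual behaviour towards a very similar study, and it includes refusers. Completion at each stage adds to it. For the platform, Table 3 counts missing items, drop-outs at questionnaire 2 and technical problems across the study. Convenience sampling is also ordinary in qualitative work, where depth matters more than the fraction sampled, and limiting the interview to the experimental arm makes sense for questions about the video.

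Much of this stands, and it rules out several stronger readings that a reader might infer:
- *That the platform objective rests on volunteers.* It does not. Satisfaction is one measure under that objective, and the others cover all participants.
- *That these aims could only return a favourable answer.* The interviews are semi-structured and analysed thematically, with no yes/no threshold. Poor completion or frequent technical faults would be a negative result for the platform.
- *That parents who struggled are never heard.* Drop-outs and faults are counted, and a parent who struggled but finished can volunteer and say so.
- *That inviting only the experimental arm to interview, before questionnaire 2, raises that arm's retention.* Nothing in the protocol shows this. No interview incentive is described, reminders are not described as differing by arm, and an interview could equally be felt as a burden.

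What the defence does not answer is the willingness aim itself. Consent is given before any experience of the study, and for refusals only the timing is recorded. Neither shows whether parents, least of all those shown the sham video, would take part in such a study again. The reason for interviewing only the experimental arm about the video does not extend to willingness or to a platform that both arms use.

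**Conclusion.** The point holds for stated willingness and, more narrowly, for satisfaction with the platform. Direct evidence on both will come from an expected 12–20 experimental-arm volunteers who also completed questionnaire 2. It is probably biased upward, by an amount the protocol does not allow one to estimate, and it cannot be carried over to sham-arm parents, drop-outs or interview decliners. The percentages in the table are illustrations under assumed p and r, not estimates for this trial.

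The conclusion relies on Table 3 and the questionnaire contents listed under Data collection. The questionnaires themselves are in additional files that were not available. If they already hold such items for both arms, only Table 3 needs to say so. The weakness is cheap to remedy, and it leaves the pilot's other feasibility measures unaffected.

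**What to change.** At the end of questionnaire 1, in both arms, add one Likert item on willingness to take part in a similar study and one on ease of using the platform. In Table 3, enter the first under the management domain and the second under the process domain. Report both by arm with confidence intervals, alongside the consent rate, and keep the interviews to explain the answers. The interview invitation can stay where it is: moving it has no demonstrated benefit and might lose parents who would agree in the ED but not later from home.

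The cost is under a minute of extra completion time per parent, a small ethics amendment and an edit to app content that is already controlled from a central server. Two limits remain. Parents who refuse at approach are still reached only through the consent rate, and the items would be answered before the burden of follow-up has been experienced.

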### Sample size estimate

Sample size calculations are not required for pilot/feasibility studies as hypothesis testing is not the focus of this research design [32, 33]. Rather, recruitment will take place over a 6-month period and will be evaluated as part of the identified process outcome measures. This 6-month period is intended to reflect the seasonal nature of viral gastroenteritis, the most common cause of infection, in temperate climates [34]. Recruitment will take place over the peak infection time of late winter [34]. The study site has approximately 500 patients presenting with symptoms of AGE over a 6-month period.

Philosophically, qualitative methods do not conduct prospective determinations of a sample size; instead, an adequate sample permits a deep, case-oriented analysis that results in a new understanding of experience [35]. In this study, convenience sampling will be used to recruit participants. It is anticipated that 12–20 interviews will be sufficient to see patterns in experiences [36].

### Data collection

Participants will be provided with disposable headphones and an iPad containing the iCare Adventure electronic platform. iCare Adventure is a client-server based e-therapeutics platform designed to expedite and improve the management of patients’ care within pediatric ED facilities. iPads, which are locked to the iCare Adventure app, are given to parents participating in research in the ED. All content within the app, including screen flow, textual content, images, videos, protocols, and questionnaires, is controlled on a centralized server. When the application restarts, it calls to the server, the iPads report all user interactions back to the server in real time, and the server can dynamically create real-time reports of the aggregated data. Data collection processes and forms will be piloted with the research team prior to the start of data collection.

The informed consent process and quantitative data collection will be completed on iCare Adventure, and participants will be automatically given the questionnaires and appropriate intervention (i.e., whiteboard video or sham video) based on the randomization sequence. A unique study identifier will be generated for each participant within the iCare Adventure platform. All data collection points will be electronically time-stamped.

As part of the post-intervention questionnaire 1, participants receiving the experimental intervention will be asked about their willingness to be contacted later for an individual, in-depth, semi-structured, qualitative interview. If interested, they will provide contact information (i.e., name, phone number, and best time to contact) and a member of the research team will follow up via telephone.

Using a qualitative descriptive approach [37, 38], a semi-structured interview guide will be used. This data collection strategy will be used to obtain all information required, probe participants’ responses, and give participants freedom to respond and illustrate concepts in an open-ended fashion [36]. Interview questions will move from the general to the specific, with interviews later in the data collection period becoming increasingly more focused [39]. Interviews will be conducted in-person or over the telephone and will be audio recorded. Audio recordings will be anonymized, de-identified, and transcribed verbatim by a third party contractor. Transcriptionists will sign a confidentiality agreement.

The following data will be collected over the course of this study:Pre-intervention questionnaire (baseline, see Additional file 1): Participants will complete a pre-intervention questionnaire that includes demographics, knowledge questionnaire, and Decision Regret Scale within the iCare Adventure platform on the iPad.**Participants will then be randomized to view the study intervention or the standard care intervention within the iCare Adventure platform on the iPad. This process will be seamless for the participants.Post-intervention questionnaire 1 (immediate, see Additional file 2): After viewing the intervention, participants will complete the knowledge questionnaire and Decision Regret Scale a second time. In addition, participants will complete two items assessing their own performance on the knowledge questionnaire and Decision Regret Scale and one item regarding the perceived value and benefit of the KT tool. They will also be asked if they would like a video link emailed to them. At the end of this questionnaire, parents will be informed that the post-intervention questionnaire 2 will be emailed to them 4 days after this ED visit for completion at their earliest convenience. Experimental intervention group parents will be asked about participation in a qualitative focus group at this time.Post-intervention questionnaire 2 (4–14 days post-ED, see Additional file 3): Participants will be emailed a secure link on day 4 post-ED discharge to complete the knowledge questionnaire and Decision Regret Scale a third time, two items assessing their own performance on the knowledge questionnaire and Decision Regret Scale, three items related to healthcare utilization, and three items related to the perceived value and benefit of the KT tool (if applicable). Reminders to complete post-intervention questionnaire 2 will be sent to those who have not completed the survey every third day (day 7, 10, 13) to complete the survey by day 14 post ED-discharge. Previous research has demonstrated that 82% of AGE cases are resolved in 3 days or less and 14 days [40] represents the outer limit for pediatric AGE resolution [41].Post-intervention semi-structured interview (sub-sample of experimental group, see Additional file 4): Participants in the experimental group indicating willingness to participate in an in-depth, semi-structured, qualitative interview will be contacted via telephone after completion of post-intervention questionnaire 2. Up to three phone calls will be made to establish interview date/time. Qualitative interviews will focus on satisfaction with iCare Adventure platform, perceived benefit and value of the KT intervention, and willingness to participate in future, similar research.
